## Abstract

**Background:**

Neuroplasticity-based approaches seem to offer promising ways of maintaining cognitive health in older adults and postponing the onset of cognitive decline symptoms. Although previous research suggests that training can produce transfer effects, this study was designed to overcome some limitations of previous studies by incorporating an active control group and the assessment of training expectations.

**Objective:**

The main objectives of this study are (1) to evaluate the effects of a randomized computer-based intervention consisting of training older adults with nonaction video games on brain and cognitive functions that decline with age, including attention and spatial working memory, using behavioral measures and electrophysiological recordings (event-related potentials [ERPs]) just after training and after a 6-month no-contact period; (2) to explore whether motivation, engagement, or expectations might account for possible training-related improvements; and (3) to examine whether inflammatory mechanisms assessed with noninvasive measurement of C-reactive protein in saliva impair cognitive training-induced effects. A better understanding of these mechanisms could elucidate pathways that could be targeted in the future by either behavioral or neuropsychological interventions.

**Methods:**

A single-blinded randomized controlled trial with an experimental group and an active control group, pretest, posttest, and 6-month follow-up repeated measures design is used in this study. A total of 75 cognitively healthy older adults were randomly distributed into experimental and active control groups. Participants in the experimental group received 16 1-hour training sessions with cognitive nonaction video games selected from Lumosity, a commercial brain training package. The active control group received the same number of training sessions with The Sims and SimCity, a simulation strategy game.

**Results:**

We have recruited participants, have conducted the training protocol and pretest assessments, and are currently conducting posttest evaluations. The study will conclude in the first semester of 2017. Data analysis will take place during 2017. The primary outcome is transfer of benefit from training to attention and working memory functions and the neural mechanisms underlying possible cognitive improvements.

**Conclusions:**

We expect that mental stimulation with video games will improve attention and memory both at the behavioral level and in ERP components promoting brain and mental health and extending independence among elderly people by avoiding the negative personal and economic consequences of long-term care.

**Trial Registration:**

Clinicaltrials.gov NCT02796508; https://clinicaltrials.gov/ct2/show/NCT02796508 (archived by WebCite at http://www.webcitation.org/6nFeKeFNB)

## Introduction

### Background

Neurocognitive frailty is the biggest threat to successful aging [1]. There is overwhelming evidence that the number of inflammatory mediators increases vastly in pathological aging [2] and in healthy aging as well [3]. This inflammation has a negative impact on cognition [4]. C-reactive protein (CRP), an acute-phase protein of hepatic origin that increases following interleukin-6 secretion by macrophages and T cells, has been identified as a hallmark of systemic inflammation, and it can be assessed by noninvasive methods in saliva [5]. A key challenge that faces the aging society is to find new approaches to understand the aging mind and brain that could enhance successful, optimal aging [6]. Another major challenge is to understand the factors that could reduce or delay the negative consequences of age-related cognitive decline [7]. The idea behind this randomized controlled trial (RCT) is that cognitive abilities could be strengthened by interventions that promote positive brain plasticity [8].

Normal aging is associated with gray and white matter shrinkage. The lateral prefrontal cortex, cerebellum, and medial temporal lobe system including hippocampus are affected. Minimal reduction occurs in the entorhinal and occipital cortices [1,9,10]. These brain changes are associated with declines in several important cognitive functions, including processing speed, executive functions, working memory, and episodic memory [11-14]. However, other crystallized abilities such as general knowledge, verbal abilities [15-17], and implicit memory [18,19] are mostly preserved. Older adults with mild cognitive impairment [20] and Alzheimer disease patients have shown preserved implicit memory despite huge deteriorations in episodic memory [21,22]. Although behavioral priming for repeated pictures is spared in older adults, reduced neural activation, which is a signature of implicit memory, is affected. The relationship between brain function and behavior found in young adults is altered in older adults, although these age-related changes do not affect behavioral facilitation. These findings have implications for the notion that automatic processes, previously considered preserved with age, are susceptible to the effects of aging at the neural level. The age-invariant behavioral facilitation with stimulus repetition is observed as a result of more sustained neural processing of visual stimuli in older adults as a form of compensatory neural activity [23].

Electrophysiological studies have also found significant age-related event-related potential (ERP) changes in brain activity associated with memory retrieval in spite of similar performance in young and older adults [24]. Elders compensate for their lower level of parieto-occipital functioning as shown by smaller P300 amplitude at posterior sites by recruiting frontal sites as a mode of brain adaptation [25]. In touch, despite similar behavioral performance in a recognition memory task involving familiar 3D objects, young and older adults recruited different neural resources to perform the task. Age-related differences were found in brain oscillations, as measured by event-related spectral perturbations (ERSPs), suggesting the recruitment of additional neural resources as shown by greater alpha and beta power reductions in older adults [26]. Despite similar behavior performance, normal aging was found to affect ERPs and oscillatory brain activity during an incidental speeded haptic symmetry detection priming task. However, the young adults showed more positive amplitude than the older adults in the alpha and beta bands from stimulus onset [27]. All these neural results suggest that the older brain adapts in order to maintain the same level of performance as the younger brain both in explicit and implicit memory tasks.

Neural plasticity exists at several levels of the neural substrate [28,10], although not to the same degree in older as in younger adults [15,29,30]. These findings suggest that the aging brain retains some neuroplasticity, which can be influenced by the individual’s behavior. The prolonged mismatch between functional organismic supplies and environmental demands produces cognitive plasticity and underlines the capacity of the brain to implement behavioral flexibility [31]. Although there are personal factors, human behavior can change with appropriate training as the brain reorganizes in response to the environment [32]. Based on the idea of neuroplasticity, different types of interventions have been developed to ameliorate cognitive and functional declines by strengthening social networking using new information and communication technology (ICT) [33-35] and cognitive skills training [36,37] and promoting an active lifestyle [38,39] and physical activity training [40,41].

As people age, they experience declines in attentional control, mediated by the dorsolateral prefrontal cortex, and in long-term memory functions, mediated by the medial temporal lobe and the hippocampus. These areas suffer the highest degree of age-related atrophy [9]. Moreover, the prefrontal cortex facilitates the organization and contextualization of incoming information and interacts with the hippocampus during working memory implementation [42,43]. This relationship is strengthened with age [44]. These findings are especially relevant due to the existing links between these basic cognitive abilities and everyday functioning. The malfunction of these basic abilities is a significant predictor of older adult difficulties with the instrumental activities of daily living, leading to loss of independence [45,46]. Therefore, it is of vital importance to pursue the question of whether cognitive decline can be reversed or delayed through cognitive training interventions [47].

Video games and other computerized programs are receiving increasing interest from cognitive and neuroscientists to investigate the possibility of transfer to untrained tasks [48-50]. Researchers are increasingly using new technology, including cognitive training platforms and video games, to investigate their impact on cognition [48-52]. Computer-based interventions have the advantage that they can be easily used by elderly people living either at home or in nursing homes and could be a good alternative to traditional training programs [53]. This RCT aims to assess the effectiveness of training older adults with digital nonaction video games.

Two challenges must be overcome in order to develop an effective cognitive aging intervention [54-55]: (1) transferring training gains to untrained tasks and (2) designing interventions that encourage compliance. Older adults prefer games that involve mental challenge [56-57], while studies with young adults have shown that fast-paced action games result in broader transfer effects. A “first-person shooter” video game is not an appropriate choice for older adults [58]. Nonaction video games have potential advantages as they are enjoyable, low-cost, and can be self-administered. Recent results from a systematic review [53] and meta-analyses [59-61] suggest that training elders with video games improves information processing, with unexpected larger effects in old-older adults than in young-older adults. Moreover, the results of a recent meta-analysis of action video game training showed that healthy adults benefit from training in overall and specific cognitive domains, but young adults benefit more than older adults [62]. These findings underscore the potential of video game training as an effective intervention tool for cognitive improvement. Results of studies on executive function and working memory are less consistent. It is possible that nonaction video games are not an effective means of improving or maintaining these functions in older adults. Games provide an enjoyable way of passing the time and of giving meaning to the day [56]. In short, video games can offer important benefits to older adults, bearing in mind that intervention compliance is a key factor in longitudinal training studies [54].

A previous RCT conducted in our laboratory investigated the effects of nonaction video game training on a series of cognitive functions that decline with age and subjective well-being. Two groups of older adults participated in the study: an experimental group that received the training and a noncontact control group. Groups were similar at baseline on demographics, vocabulary, global cognition, and depression status. The results showed improvements in the video game–trained group and no change in the passive control group in processing speed, attention, and immediate and delayed visual recognition memory and a trend to improve in 2 dimensions of the Well-being Scale (affection and assertivity) [63]. However, visuospatial working memory and executive control (shifting strategy) functions did not improve [49,64,65].

A recent longitudinal intervention study conducted to investigate the effects of video game training in healthy older adults showed that 15 1-hour training sessions with 6 nonaction video games produced significant improvements on 2 visuospatial working memory tasks and on episodic and short-term memory tasks. Some of these gains were maintained over a 3-month follow-up period [52]. In both previous studies, experimental groups were compared with passive control groups. To better attribute training-related improvement to the intervention and to avoid placebo effects [66], the current RCT compares performance on a series of attentional and visuospatial working memory tasks of an experimental group trained with selected nonaction video games from the commercial Lumosity computerized training program (www.lumosity.com) with that of an active control group carrying out the same number of training sessions with The Sims, a simulation strategy game in which the player takes control of the life of a character in everyday activities, and SimCity, a life simulation game in which the player is the mayor of a city that he or she must develop. Both groups used a mobile tablet device during the training sessions. These video games were chosen to train the active control group because this group should also play with engaging and challenging video games the same training hours, potentially equating the social contact experienced during training by experimental and active-control groups.

Training expectation is an important issue in cognitive training studies [51,67]. To address this issue, participants report their expectations (increase or decrease) regarding their task performance for any assessment task on a 5-point Likert-type scale. After training sessions 1, 8, and 16 (final), participants respond to training feedback questions about engagement and motivation for each training game. The objective was to find out whether both groups were similarly engaged and motivated during training.

In sum, the growth of ICT-based tools, along with their progressive implementation in all social groups, offers a great opportunity to develop low-cost preventive intervention programs able to reach the entire population. This can contribute to improving the quality of life of elderly people, with a substantial reduction in health care costs related to the loss of autonomy and independence in this population group [68]. In this RCT we investigate not only possible cognitive improvement in healthy older adults in selected cognitive domains that decline with aging but also possible neural changes of training using electrophysiological methods at pre- and posttraining and 6-month follow-up. The study also explores neuroinflammatory mechanisms underlying possible cognitive training-induced effects using noninvasive saliva-testing methods.

### Objectives and Hypotheses

The study has 3 main complementary objectives:

1. To examine the behavioral and electrophysiological effects of training older adults with nonaction video games on a series of cognitive tasks designed to assess attentional functions (mainly response inhibition, distraction, and alertness) and to maintain and update verbal and visuospatial working memory. We are also interested in investigating the sustainability of the transfer effects after a 6-month no-contact period.

2. To explore whether motivation, engagement, or expectations account for possible training-related improvements.

3. To examine whether inflammatory mechanisms assessed with noninvasive measurement of CRP in saliva impair cognitive training-induced effects. Inflammatory parameters in the participants obtained by noninvasive saliva-testing methods will be analyzed in biochemical assays to study their possible correlations with cognitive abilities.

We hypothesize that participants in the Lumosity group will improve selective attention assessed with oddball and Stroop tasks and working memory assessed with Corsi blocks and *n*-back tasks in comparison with participants in the active control group. From an electrophysiological perspective, we also hypothetize that in the oddball task the cognitive video game–trained group will improve both the ability to return attention to the relevant task after having been distracted by the novel stimulus (reorientation negativity [RON]) and the ability of the brain to pay attention to the novel stimulus (P300).

Intervention studies conducted with older adults have focused mostly on training a given cognitive function and then measuring the improvement in that function [69,29] and less often on possible changes in neural activity after training [70,71]. Based on the idea that the older human brain still has some plasticity (the ability to change in response to external stimulation), our main hypothesis is that training older adults with appropriate, adapted, and motivating nonaction video games will transfer to cognitive functions that decline with age, such as attention and working memory, by improving these pillars of cognition, which are crucial to maintaining independent living and cognitive health in old age.

## Methods

### Overview of the Study Design

A 2-arm, parallel-design RCT [72] was designed to evaluate the effectiveness of video game training to promote cognitive and brain health in older adults. Figure 1 shows the Consolidated Standards of Reporting Trials flow diagram of the study. This RCT is being conducted in Madrid, Spain, with an allocation ratio of 1:1 to evaluate the influence of training with nonaction video games on attention and memory functions. The design was a single-blind design. Eligible participants were randomized using a computer algorithm into intervention (cognitive nonaction video game training) or active control (life-simulation games) groups. Researchers were not blind to treatment allocation. The Universidad Nacional de Educación a Distancia (UNED) Institutional Review Board approved the study protocol. All participants provided written informed consent.

**Figure 1 figure1:**
[figure not shown]
The Consolidated Standards of Reporting Trials flow diagram.

### Eligibility and Exclusion Criteria

All participants live independently with normal or corrected-to-normal hearing and vision and are free of neurological or psychiatric disorders or traumatic brain injury. To determine their eligibility, each participant completed a screening battery consisting of the Mini-Mental State Examination (cut-off score 26) [73] to rule out possible cognitive impairment, the Yesavage Depression Scale (cut-off score less than 5) [74], and the Information subscale of the WAIS-III scale (normal score) [75]. Exclusion criteria were a diagnosis of dementia, cognitive impairment (score of <26 on the Mini-Mental State Examination), depression, less than 20/60 vision with or without correction, inability to complete the study activities, communication problems, or current plans to move to another city. All participants were healthy volunteers.

### Sample Size

The sample size is based on the number of observations needed to compare the 2 groups of gamers, those trained with Lumosity and those trained with The Sims. As we do not have standard deviations of the scores in our main dependent variables, we used G*Power 3.1 (Department of Psychology) to compute the number of participants, using analysis of variance as a statistical test. For this, using a power of .80, effect size of 0.50, an alpha level of .05, and 2 groups within the *F* test family, we obtained a required total sample size of 57. With a dropout rate of 10%, a total of 63 participants would be required. Rounding up the numbers, we would need more than 64 participants (32×2). As the flow diagram shows, the final number of participants matches these a priori computations closely: 38 participants were assigned to the experimental group (8 lost at posttest) and 37 to the control group (12 lost at posttest).

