
### General Procedure

Participants in the study were randomly assigned to the cognitive nonaction video game training group or the noncognitive game training active control group. The introduction of an active control group is necessary to avoid placebo effects [54]. Based on the results of our meta-analytic study [61], we use training regimes that are not too long to avoid loss of motivation, and simple, nonaction games that appeal more to elders. According to the temporal discount hypothesis [85], future rewards are less valuable than inmediate rewards. In each session, the trainees play 10 nonaction video games from Lumosity, described below.

The main question examined in our study is whether group (experimental group, active control group) interacts with testing session (pretest, posttest, and follow-up) with regard to performance on a series of cognitive tasks. At least 2 measures for each cognitive domain are acquired to examine transfer of training to untrained tasks demanding attention and working memory. We selected these cognitive domains because these functions deteriorate with aging and tax functions that are critical for independent living. To explore the underlying neural mechanisms of successful transfer of training gains to attentional mechanisms (alert, distraction, and inhibitory effects) and executive control (spatial working memory), electrophysiological data (ERPs) are recorded at pretraining (T1), posttraining (T2), and 6-month follow-up (T3).

All the methodological designs of the primary outcome measures have been constructed using the rules of counterbalancing and stimulus rotation. Response keys are counterbalanced across conditions. The computerized tasks have been programmed using E-Prime 2.0 (Psychology Software Tools Inc). All the statistical analyses of the behavioral results will be performed using SPSS (IBM Corp) and results will be considered significant at *P*<.05, with Bonferroni-corrected post hoc tests performed as appropriate. Continuous EEG activity are recorded in our laboratory with thin electrodes from 34 scalp sites using a NuAmps amplifier as mentioned before.

After randomization and initial assessment (baseline), participants were invited to attend the University Center of Escuelas Pias in Madrid to perform the training sessions in small groups. Trained and active control groups followed 16 training sessions carried out on different hours and days that lasted approximately 10 to 12 weeks.

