
#### Effects of Training on Spatial Working Memory

##### Overview

To investigate whether training transfers to improvements in spatial working memory, the participants perform a computerized Corsi blocks task. Recent meta-analytic studies conducted with trainees from childhood to older adults [60] and with older adults [61] found negligible effects of video game training on executive functions. The absence of improvement after training may depend on the specific kind of video games used. Studies that used first-person shooter action games reported benefits after training [103,104]. This type of game requires great perceptual abilities, preparedness for unpredictability, and strong emphasis on peripheral visual processing [105]. However, older adults do not like this type of game [55]. Previous findings from our lab yielded mixed results. One study [49] showed no transfer to working memory tasks, while a second study [52] showed that the trainees’ performance improved significantly after training in 2 visuospatial working memory tasks, the Corsi blocks and the jigsaw puzzle. Our results contrast with those of Nouchi et al [88] who found improvements in executive functions after training for 5 weeks. The ineffectiveness of training in spite of the fact that several of the nonaction video games mimic working memory tasks is in line with the findings of Boot and colleagues [54]. Due to these mixed results, the aim of this RCT is to find out whether training effects transfer to the spatial working memory of older adults.

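### The stated .80 power is tied to a comparison of 2 groups and is not shown to apply to the group × session test on which the trial rests

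*Protocol article*

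**What the plan says.** Sample Size in the protocol article sets out the purpose of the calculation: "The sample size is based on the number of observations needed to compare the 2 groups of gamers". It explains that "we do not have standard deviations of the scores in our main dependent variables", so G*Power was run "using analysis of variance as a statistical test". The inputs are given as "using a power of .80, effect size of 0.50, an alpha level of .05, and 2 groups within the" F test family, with the result "we obtained a required total sample size of 57". A dropout allowance follows: "With a dropout rate of 10%, a total of 63 participants would be required". The section then reports 38 and 37 participants assigned, with 8 and 12 lost at posttest, which leaves 30 and 25.

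Other sections describe a different test. General Procedure states the main question as "whether group (experimental group, active control group) interacts with testing session (pretest, posttest, and follow-up"). The oddball section predicts a group × session interaction. Results plans an analysis of variance with 2 groups at 3 time points. The closing summary of the working memory outcomes defines the primary outcomes, on four tasks, as posttest performance better than pretest.

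**The concern.** A comparison of 2 groups on one score and a group × session interaction are different tests. The interaction depends on how strongly a person's scores correlate between visits (rho). With equal variances, the variance of a pretest-posttest change is 2(1 − rho) times that of a single score. On a raw-score effect size, the two tests therefore have the same power only at rho = 0.5. The interaction is weaker below that value and stronger above it.

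Sample Size gives neither rho nor the number of sessions, and does not say which score the 0.50 is measured on. A reader would naturally take .80 as the chance of detecting transfer on a primary task, and would weigh a null result on any of the four tasks accordingly. Nothing in the section supports that use of the figure.

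**Working it through.** **Inputs.** From Sample Size: power .80, effect size 0.50, alpha .05, 2 groups, stated N = 57, and n1 = 38 − 8 = 30 and n2 = 37 − 12 = 25 at posttest. From General Procedure and Results: 3 sessions. Not in the article, so assumed: rho = 0.3, 0.5 and 0.7; equal variances and equal correlations across visits; both readings of 0.50. All power figures are two-sided and use the noncentral F distribution.

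**1. The article's own figure.** For a 2-group analysis of variance, the noncentrality is λ = f²N with 1 and N − 2 df.
- If 0.50 is f: λ = 0.25 × 57 = 14.25, power .96. N for .80 power is 34.
- If 0.50 is d: f = 0.50/2 = 0.25, λ = 0.0625 × 57 = 3.56, power .46. N for .80 power is 128.

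Neither gives 57. Among the variants tried at f = 0.50 and power .80, 57 appeared only for an F test with 5 numerator df (.794 at N = 56, .803 at N = 57). Five df would fit 2 × 3 cells minus 1, but the article states no such choice. The interaction has (2 − 1)(3 − 1) = 2 df with within-person error, so that variant is not the deciding test either. The dropout step is not at issue: 57 × 1.10 = 62.7, which rounds up to the stated 63.

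**2. Pretest-posttest × group contrast, 30 v 25.** λ = [d² / (2(1 − rho))] × n1n2/(n1 + n2), with 1 and 53 df. Here n1n2/(n1 + n2) = 750/55 = 13.64. For example, at d = 0.5 and rho = 0.3, λ = (0.25/1.4) × 13.64 = 2.44.

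| | rho 0.3 | rho 0.5 | rho 0.7 |
|---|---|---|---|
| λ, gap 0.5 SD (0.50 read as d) | 2.44 | 3.41 | 5.68 |
| Power | .335 | .442 | .648 |
| λ, gap 1.0 SD (0.50 read as f) | 9.74 | 13.64 | 22.73 |
| Power | .865 | .952 | .997 |
| Smallest gap for .80 power (SD) | 0.91 | 0.77 | 0.60 |

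**3. Three-visit interaction, 2 df.** λ = 13.64 × S/(1 − rho), with 2 and 106 df. S is the sum of squared deviations of the three group gaps from their mean, and all 55 are assumed to return at follow-up. If the gap d is fully kept at 6 months, S = 2d²/3. If half is kept, S = d²/2.

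| Power | rho 0.3 | rho 0.5 | rho 0.7 |
|---|---|---|---|
| 0.5 SD, kept | .336 | .453 | .679 |
| 0.5 SD, half kept | .261 | .351 | .547 |
| 1.0 SD, kept | .899 | .972 | .999 |
| 1.0 SD, half kept | .793 | .914 | .992 |

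The same stated 0.50 is thus compatible with power of about .26 to above .99, depending on its metric, on rho and on how much of the gap is kept.

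**The case against.** The strongest reply is that a 2-group comparison of change scores is the pretest-posttest × group interaction. If 0.50 is standardised on change, the 2-group formula is the right one at every rho, and the primary outcome is indeed worded as change. This stands as algebra, and it rules out saying that the 2-group formula can never serve. But Sample Size does not say that 0.50 refers to change, and it speaks only of SDs of the scores. Even on that reading, N = 57 gives .96 or .46, not .80.

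Three stronger inferences are tempting, and the article supports none of them.
- A reader might conclude that the trial is underpowered. The low figures hold only if 0.50 is a raw-score SD difference. Read as f, which is natural in an F-test calculation, most of the figures exceed .80.
- A reader might say the SDs were available all along, since the laboratory's earlier study found that "performance improved significantly after training in 2 visuospatial working memory tasks, the Corsi blocks and the jigsaw puzzle". That bears on Corsi blocks only, one of four primary tasks, and nothing shows that the earlier scores share the present version's scale. The pretests of this trial came after the a priori calculation, and pretests alone cannot supply rho.
- A reader might expect low between-visit correlation for Stroop interference and negative priming because they are difference scores. The article says nothing on this.

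Finally, a condensed article may leave correlation inputs for each task to a fuller document. That is fair, and their absence alone would be no finding. The point is that the justification actually printed names a different comparison from the declared main question.

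**Conclusion.** The point holds in a limited form. The article ties .80 power to a 2-group comparison while resting its conclusions on group × session and on pretest-to-posttest change, so the .80 is not shown to apply to the deciding test. It could be carried over to the pretest-posttest contrast only if 0.50 were defined on change scores, which the section does not do. The pairing of .80 with N = 57 also matches no 1-df 2-group test under either metric.

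How far the true power lies from .80 cannot be settled from the article. For the pretest-posttest contrast with 30 v 25, it is about .335 to .65 at a 0.5 SD gap and about .87 to above .99 at a 1.0 SD gap, for assumed rho of 0.3 to 0.7. The finding concerns a figure that readers will rely on. It is neither a demonstration of inadequate size nor a reason to doubt the planned analysis itself.

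**What to change.** Rewrite the power statement in Sample Size as follows.
- Name group × pretest-posttest as the powered contrast.
- Define 0.50: f or d, and raw score or change.
- Replace the .80 statement with the power, or the smallest detectable difference, of that contrast for the 30 and 25 participants left at posttest, over a stated range of rho. For .80 power the detectable gap is about 0.91, 0.77 and 0.60 SD at rho 0.3, 0.5 and 0.7.
- Keep the sentence about unavailable SDs as the reason for the a priori calculation. If wanted, add pretest SDs pooled over both arms, to put the detectable difference on each task's own scale.

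The cost is one paragraph and a short calculation, with no change in enrolment. The downside is that the stated power may become less favourable.
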